### 11.3 Statistical criteria of termination of trial

Premature termination of the trial based on statistical criteria is not foreseen. In case of serious adverse events that are assessed as related to the study drug, the decision regarding premature trial termination is at the discretion of the Sponsor.

### 11.4 Planned Analyses

#### 11.4.1 Datasets to be analysed, analysis populations

The full analysis set (FAS) will include all patients that have been randomized to one of the two treatment arms. The SG analysis set (SGAS) will include all patients with successful Sleeve Gastrectomy. The RYGB analysis set (RYAS) will include all patient with successful Roux-en-Y gastric bypass surgery. PK/PD analysis will be performed on a subset of the SG and RY patients (16 patients each). Data will be presented combined as well as for patients with SG and RYGB.

#### 11.4.2 Demographic and baseline characteristics

Patient characteristics will be presented as frequency and percentage for binary variables, mean and standard deviation for continuous, normally distributed variables, and median and interquartile range for continuous, non-normally distributed variables.

#### 11.4.3 Primary Analysis

The primary analysis is an intention-to-treat analysis (ITT), i.e. all patients (FAS) will be analysed in the group they were originally allocated to. The primary binary outcome (i.e. the proportion of 28-day VTE in both treatment arms within 28 days after bariatric surgery) will be evaluated descriptively in each group presenting proportions with 95% Wilson confidence intervals. Additionally, we will compare the primary binary outcome using a Cochran-Mantel-Haenszel-test stratified for the stratification factors used in the randomization. These tests will be exploratory, not confirmatory.

#### 11.4.4 Secondary Analyses

Secondary analyses will be performed per protocol (PP), i.e. only patients that in fact received the study treatment according to the randomization will be analysed. Secondary analyses will be reported for the FAS, the SGAS and the RYAS.

Following secondary outcomes will be analysed:

- Symptomatic VTE within 28 days after bariatric surgery
- Asymptomatic VTE within 28 days after bariatric surgery
- All-cause mortality within 28 days after bariatric surgery
- Postoperative morbidity (Dindo-Clavien classification) within 28 days after bariatric surgery
- VTE-related death within 28 days postoperatively
- PK/PD (subset of 32 patients)

The secondary binary outcomes will be evaluated descriptively in each group presenting proportions with 95% Wilson confidence intervals. Additionally, we will compare the secondary binary outcomes using a Cochran-Mantel-Haenszel-test stratified for the stratification factors used in the randomization. These tests will be exploratory, not confirmatory.

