### **7.4.2 Criteria for withdrawal/ discontinuation by the investigator**

Patients can be withdrawn by the investigator in the following situations:

- Leakage of the anastomosis after bariatric interventions, staple line leakage, major bleeding or thrombotic complication or other relevant medical condition in which continuation of study is not possible or reasonable as assessed by the principal investigator
- Patient non-compliance

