### **8.2 Administration of experimental and control interventions**

#### **8.2.1 Experimental Intervention**

Study drug will be applied as peroral medication at the indicated time points after bariatric surgery. Arm A: Thromboprophylaxis with rivaroxaban 10 mg QD for 7 days after bariatric surgery.

Arm B: Thromboprophylaxis with rivaroxaban 10 mg QD for 28 days after bariatric surgery.

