#### **9.3.5 Procedure in case of confirmed VTE (symptomatic and asymptomatic)**

In patients with confirmed VTE, study drug will be stopped and patient will be treated according to current guidelines for the respective VTE [39].

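### The secondary analyses are assigned to both a per-protocol set and all randomised patients, and a per-protocol set requiring the full allocated course would favour the 28-day arm

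*Protocol*

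**What the plan says.** Section 11.4.4 makes the secondary analyses per protocol, so that "only patients that in fact received the study treatment according to the randomization will be analysed". The synopsis (Statistical Considerations) repeats this rule and does not mention the FAS. The next sentence of 11.4.4 reads: "Secondary analyses will be reported for the FAS, the SGAS and the RYAS". Section 11.4.1 defines that set without exclusions: "The full analysis set (FAS) will include all patients that have been randomized to one of the two treatment arms".

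The secondary clinical outcomes in 11.4.4 are symptomatic VTE, asymptomatic VTE, all-cause mortality, morbidity and VTE-related death, each over 28 days.

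Section 8.2.1 gives both arms the same drug and dose for different lengths of time: "Arm A: Thromboprophylaxis with rivaroxaban 10 mg QD for 7 days after bariatric surgery" and "Arm B: Thromboprophylaxis with rivaroxaban 10 mg QD for 28 days after bariatric surgery". Section 9.3.5 says "In patients with confirmed VTE, study drug will be stopped". Section 7.4.2 lets the investigator withdraw a patient for several reasons, among them "major bleeding or thrombotic complication or other relevant medical condition".

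**The concern.** There are two problems, and the second follows from the first.

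First, one section names two different sets for the same analyses. A per-protocol set leaves some randomised patients out; the FAS leaves out none. As written, the main set for every secondary clinical outcome is undetermined.

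Second, the per-protocol rule does not say how to classify a patient whose drug was stopped because of an outcome event. Since duration is the only difference between the arms, the natural test of treatment according to randomisation is whether 7 or 28 days were received. Under that test, a long-arm patient with a symptomatic VTE on day 15 stops drug and fails. A short-arm patient with the same event on the same day finished on day 7 and passes. Exclusion then depends on the outcome and falls unevenly on the arms, in favour of the extended course. The outcomes exposed are symptomatic VTE, the two mortality outcomes, and morbidity to the extent that a complication ends treatment.

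This matters because a secondary objective (section 4.3) is to compare the two durations on thromboembolic events, and section 3.1 says the results will help design phase III trials.

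**Working it through.** **The plan's own figure.** Section 11.2 gives expected 95% Wilson intervals of 0.1–3.7% (true rate 0.5%, long arm) and 2.4–10.1% (true rate 5%, short arm) with 130 patients per arm. Averaging the Wilson interval exactly over a binomial with n = 130 gives 0.12–3.72% and 2.44–10.14%, so these reproduce. The expected numbers of VTE of any kind are 130 × 0.005 = 0.65 in the long arm and 130 × 0.05 = 6.5 in the short arm. The chance of no long-arm event is 0.995^130 = 52%. With counts this small, reclassifying one or two patients is visible.

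**Who is removed if the full course is required**

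| Event | Short arm (7 days) | Long arm (28 days) |
|---|---|---|
| Symptomatic VTE or death before day 7 | removed | removed |
| Symptomatic VTE or death, days 8–27 | kept | removed |
| Asymptomatic VTE found at V7 (day 28±2) | kept | largely kept |

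The last row follows from section 9.4.14, which defines asymptomatic DVT by the V7 ultrasound, and section 9.4.10, which makes V7 the long arm's end-of-treatment visit. A V7 held on day 26 or 27 could be a small exception.

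**Size for symptomatic VTE with no true difference.** Let p be the true rate in both arms and g the share of events after day 7. The protocol does not give g; I assume 30% to 90%. I take p = 2% as an illustration and show 1% to 3%, the range that section 3.1 gives for symptomatic DVT.

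- Long arm per protocol: every symptomatic event before the end of the course removes the patient, so the rate is about 0.
- Short arm per protocol: p·g / (1 − p·(1 − g)).

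For p = 2%:

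- g = 0.3: 0.006 / 0.986 = 0.61%
- g = 0.5: 0.010 / 0.990 = 1.01%
- g = 0.7: 0.014 / 0.994 = 1.41%
- g = 0.9: 0.018 / 0.998 = 1.80%

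For p = 1% the ends are 0.003 / 0.993 = 0.30% and 0.009 / 0.999 = 0.90%. For p = 3% they are 0.009 / 0.979 = 0.92% and 0.027 / 0.997 = 2.71%.

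**In patients.** At p = 2%, each arm of 130 expects 2.6 symptomatic events. The short arm keeps 2.6 × g, which is 0.8 (g = 0.3) to 2.3 (g = 0.9). The long arm keeps about none. The spurious difference is therefore about 1 to 2 patients.

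**On the FAS, or on a looser per-protocol reading.** If all randomised patients are analysed, both arms keep the expected 2%. The same holds if a patient who stopped because of an event still counts as treated according to the allocation. The bias comes entirely from a completion requirement.

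**The case against.** A reader might infer that long-arm event patients are removed by construction, that the long-arm rate becomes zero whatever the truth, and that deaths disappear from the long arm. The documents do not support this. Section 11.4.4 sets no minimum duration, number of doses or completion rule. A long-arm patient who stops at VTE has done what section 9.3.5 requires and can fairly be called treated according to the randomisation. Detailed per-protocol criteria are also often left to a statistical analysis plan, which is not at hand.

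The events also stay visible elsewhere. Symptomatic VTE is part of the primary composite, analysed by intention to treat on the FAS (11.4.3), and that comparison also serves the secondary objective on thromboembolic events. The safety analysis uses the FAS (11.4.6), and all-cause mortality is a listed safety variable (5.4). Major bleeding is the primary safety endpoint and is not among the 11.4.4 outcomes. Withdrawal under 7.4.2 is optional, so complications that do not end treatment are untouched. The tests are exploratory, and a difference of 1 to 2 patients lies within the Wilson interval for 0 of 130 (0–2.9%).

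Most of this stands, and it limits the point to a possible bias in descriptive secondary estimates. Two things remain. The conflict between per protocol and FAS is on the page and needs no interpretation. And because treatment is the same in both arms until day 7, the looser reading would exclude few patients and add little to intention to treat, so the full-course reading is the more natural one. Nothing in the protocol rules it out, and the trial is open label, so the choice should not be left until data have accrued.

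**Conclusion.** The point holds in limited form, as something that should be fixed. Section 11.4.4 contradicts itself on the analysis set, and it leaves open a per-protocol rule that would select on the outcome in favour of the extended arm.

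On the full-course reading, with the same true 2% rate of symptomatic VTE in both arms and 30% to 90% of events after day 7 (both assumptions), per protocol would show about 0.6–1.8% in the short arm against about 0% in the long arm. Deaths on days 8 to 27 would be handled in the same uneven way in the per-protocol mortality outcomes, though they remain in the FAS safety analysis. The effect on morbidity cannot be sized from the protocol. On the looser reading there is no such bias.

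**What to change.** In section 11.4.4 and the synopsis:

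- Make intention-to-treat on the FAS the main analysis for all secondary clinical outcomes, with results by procedure (SGAS, RYAS) presented alongside.
- Keep per protocol as a sensitivity analysis. Judge adherence only up to the first outcome event, death or the end of the allocated course, whichever comes first, so that stopping because of an outcome event does not exclude a patient.
- Remove the wording that assigns one analysis to both the per-protocol set and the FAS, so that 11.4.4, 11.4.1 and the synopsis agree.

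This concerns analysis sets only and leaves the treatment and stopping rules as they are. It costs wording, with no new data and no change in sample size. The downside for the sponsor is that the extended arm's secondary results may look slightly less favourable than under a full-course per-protocol set.

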#### *Analysis of pharmacokinetic parameters (subgroup of 32 patients; 16 SB, 16 RYGB)*

Rivaroxaban AUC,  $C_{max}$ ,  $T_{max}$  and  $C_{min}$  (24h post application) will be calculated and displayed for both surgical procedures combined and separately using the SGAS and the RYAS PK/PD subsets. To calculate and to draw the PK parameters of rivaroxaban, the software application "R" or an equivalent statistical tool will be used. Median as well as the lower and the upper quartile will be presented in a descriptive manner.

Primary analysis of rivaroxaban concentrations will be performed using the data points specified in the study flow chart. For both surgery procedures, the area under the curve (AUC) will serve as primary endpoint. To calculate and draw the pre- and post-surgery area under the curve (AUC) of rivaroxaban, the software application "R" will be used. The data of rivaroxaban AUC is assumed to be lognormally distributed [23]. Therefore, AUC data will be log transformed in order to fulfil normality assumptions. In order to test for equivalence, the equivalence bounds of 0.8 and 1.25 will be used. Analyses will be performed after closure of the database.

The geometric mean ratio (after surgery/before surgery) together with the 95% confidence interval will be estimated for the AUC. The data will be log-transformed in order to better meet normality assumptions. The

confidence interval will be presented graphically in a descriptive manner (exponentiated to bring it back to the original scale).

#### *Analysis of pharmacodynamic parameters (subgroup of 32 patients; 16 SB, 16 RYGB)*

Results of PD data (thrombin-antithrombin-complexes (TAT), prothrombin fragment (F1+2), D-Dimers, thrombin generation and prothrombin time) are displayed in tables with median and range and in graphs. PD parameters will be calculated and displayed for combined and separate for both surgical procedures using the SGAS and the RYAS PK/PD subsets.

#### **11.4.5 Interim analyses**

No interim analysis will be performed.

#### **11.4.6 Safety analysis**

All adverse events and serious adverse events will be assessed regarding relatedness to study drug and presented in tabular form indicating absolute numbers of events and percentages. The safety analysis will be performed on the FAS.

#### **11.4.7 Deviation(s) from the original statistical plan**

Deviation from the descriptive statistical analysis plan is not foreseen. In case of deviation from the original statistical plan, this will be specified in the final report.

### **11.5 Handling of missing data and drop-outs**

Missing data will be indicated accordingly and not be replaced. In case of drop-out prior to completion of study visit V8, additional study subjects will be recruited in order to reach the intended number of study participants per group.

## **12. QUALITY ASSURANCE AND CONTROL**

### **12.1 Data handling and record keeping / archiving**

#### **12.1.1 Case Report Forms**

Study data is recorded in electronic Case Report Forms (eCRFs; REDCap™) by authorized study personnel. For each enrolled study participant an eCRF is maintained. eCRFs must be kept current to reflect subject status at each phase during the course of study. All data entered in the eCRF must be documented in a source document. Participants must not be identified in the eCRF by name or initials and birth date. Appropriate coded identification must be used. The electronic database will be validated as required by the FDA regulation 21 CFR Guidance for Industry part 11.

The investigator must review all pages within the eCRF for accuracy and consistency with the protocol, and electronically sign the eCRF upon completion.

#### **12.1.2 Specification of source documents**

Source data must be available at the site to document the existence of the study participants. Source data must include the original documents relating to the study, as well as the medical treatment and medical history of the participant.

In addition to study specific source data, the electronic patient records of the hospital (incl. laboratory values) may serve as source data. No data is directly recorded in the eCRF (i.e. without source data documentation). All source data must be available at the study centre during the entire duration of the study.

#### **12.1.3 Record keeping / archiving**

All study data must be archived for a minimum of 10 years after study termination or premature termination of the clinical trial.

## **12.2 Data management**

### **12.2.1 Data Management System**

Study data is recorded in the worldwide used research electronic data capture application REDCap™. This study database is run by the Clinical Trial Unit (CTU) of the University of Bern. Data is physically stored on servers of the University of Bern that are located in Bern, Switzerland.

### **12.2.2 Data security, access and back-up**

The database servers are kept in a locked, air-conditioned server-room at the University of Bern, Switzerland. Only system and database administrators have access to these servers and back-up tapes. Data back-ups are performed on a daily basis. Back-up tapes are stored in a safe, different location. Authorized users have access to the database using a login and a personal password. Access is restricted depending on the role of the study team member (role concept: principal investigator, investigator, study nurse, monitor, statistician, administrator).

### **12.2.3 Analysis and archiving**

Data are extracted electronically from the electronic data capture system REDCap™ after closure of the database for statistical analysis. Data for statistical analysis is processed on access controlled computers of the University Hospital Inselspital, Bern, Switzerland.

All study data must be archived for a minimum of 10 years after study termination or premature termination of the clinical trial.

### **12.2.4 Electronic and central data validation**

Data is validated upon entry in the electronic data capture system (range and consistency checks) and will be validated centrally by the principal investigator or his deputy. In addition, an on-site monitoring will be performed (see below).

## **12.3 Monitoring**

On-site Monitoring will be performed by the Clinical Trial Unit Bern, [name], Bern, Switzerland or an equivalent service provider. Monitoring details (number of visits and data/documents to be monitored) will be specified in a monitoring plan before the study initiation visit.

Source data/documents must be kept accessible to monitors and questions answered during regular monitoring visits.

## **12.4 Audits and Inspections**

Study documentation and the source data/documents are accessible to auditors/inspectors (CEC and CA) and questions are answered during inspections. All involved parties must keep the participant data strictly confidential.

## **12.5 Confidentiality, Data Protection**

Study personnel has access to study related documentation and study documents (source documents and eCRF) according to his/her specific role. Access to source documents will be permitted for purposes of monitoring, audits and inspections. All involved parties must keep the participant data strictly confidential. Data protection will be based on local and national guidelines and applicable local and national law.

## **12.6 Storage of biological material and related health data**

Biological material will be stored for a maximum duration of 10 years. Study samples are only stored with the participants consent independent from the study. In case of lacking consent regarding biobanking of study samples, all biological material will be destroyed after termination of the study.

## **13. PUBLICATION AND DISSEMINATION POLICY**

The results of the study will be published in a peer reviewed scientific medical journal and may be presented

via oral communications or poster presentations during national and international meetings.

Co-authorship on any of the publications will be based on conceptual contribution to the study according to the criteria of the International Committee of Medical Journal Editors.

## **14. FUNDING AND SUPPORT**

### **14.1 Funding**

This clinical study is supported by an unrestricted grant from Bayer Pharma AG and Janssen Pharmaceuticals, Inc.

### **14.2 Other Support**

Other support for this clinical trial is not foreseen.

## **15. INSURANCE**

Insurance coverage will be provided by the Sponsor for all study centres. A copy of the insurance certificate is filed in the investigator site file/trial master file.

## 17. APPENDICES

### 17.1 Summary of product characteristics

#### Xarelto 10 mg / 15 mg / 20 mg film-coated tablets

(Abbreviated version)

This medicinal product is subject to additional monitoring.

#### Composition:

*Active ingredient:* 10 mg / 15 mg / 20 mg rivaroxaban.

*Excipients:* Microcrystalline cellulose, croscarmellose sodium, lactose monohydrate, hypromellose, sodium laurilsulfate, magnesium stearate, macrogol 3350, titanium dioxide (E171), iron oxide red (E172).

#### Indications:

*10 mg:* Prevention of **venous thromboembolism** (VTE) in adult patients undergoing elective hip or knee replacement surgery. *15 mg/20 mg:* Prevention of stroke and systemic embolism in adult patients with non-valvular **atrial fibrillation** with one or more risk factors, such as congestive heart failure, hypertension, age  $\geq 75$  years, diabetes mellitus, prior stroke or transient ischaemic attack. Treatment of deep vein **thrombosis** (DVT) and pulmonary embolism (PE), and prevention of recurrent **DVT** and **PE** in adults.

#### Contraindications:

Hypersensitivity to the active substance or any of the excipients; active clinically significant bleeding; lesion or condition if considered a significant risk for major bleeding; concomitant treatment with any other anticoagulants except under the circumstances of switching therapy to or from rivaroxaban or when unfractionated heparin is given at doses necessary to maintain an open central venous or arterial catheter; hepatic disease associated with coagulopathy and clinically relevant bleeding risk including cirrhotic patients with Child Pugh B and C; pregnancy and breast feeding.

#### Warnings and Precautions:

Clinical surveillance in line with anticoagulation practice is recommended throughout treatment. Xarelto should be discontinued if severe haemorrhage occurs. Increasing age may increase haemorrhagic risk. *Not recommended:* in patients with severe renal impairment (creatinine clearance  $<15$  ml/min); in patients receiving concomitant systemic treatment with strong concurrent CYP3A4- and P-gp-inhibitors, i.e.azole-antimycotics or HIV protease inhibitors; in patients with increased bleeding risk; in patients receiving concomitant treatment with strong CYP3A4 inducers unless the patient is closely observed for signs and symptoms of thrombosis; *not recommended due to lack of data:* in patients below 18 years of age, in patients concomitantly treated with dronedarone. 10 mg add: in patients undergoing hip fracture surgery; 15 mg / 20 mg add: in patients with prosthetic heart valves, in patients with **PE** who are haemodynamically unstable or may receive thrombolysis or pulmonary embolectomy. *Use with caution:* in conditions with increased risk of haemorrhage; in patients with severe renal impairment (creatinine clearance 15 - 29 ml/min) or with renal impairment concomitantly receiving other medicinal products which increase rivaroxaban plasma concentrations; in patients treated concomitantly with medicinal products affecting haemostasis. 10 mg add: when neuraxial anaesthesia or spinal/epidural puncture is employed; 15 mg / 20 mg add: specific dose recommendations apply for patients with moderate to severe renal impairment and in case of

DVT/PE-patients only if the patient's assessed risk for bleeding outweighs the risk for recurrent DVT/PE. In patients at risk of ulcerative gastrointestinal disease prophylactic treatment may be considered. Although treatment with rivaroxaban does not require routine monitoring of exposure, rivaroxaban levels measured with a calibrated quantitative anti-Factor Xa assay may be useful in exceptional situations. Xarelto contains lactose.

